### Objectives and hypothesis

The trial objectives are to evaluate the effect of early availability and promotion of IFA supplements on neonatal mortality, low birthweight and preterm delivery. The primary hypothesis is that in a community-based, cluster randomized controlled trial of women from rural Bangladesh, daily supplementation with 60 mg elemental iron and 400 μg folic acid starting in the first trimester of pregnancy, and sustained for at least 180 days, will reduce neonatal mortality by 25% from 33/1000 to 24.8/1000 live births compared to usual iron-folic acid supplementation programs.

The secondary hypotheses are that the early availability and promotion of IFA supplements in intervention clusters will reduce preterm delivery by 30% (15% in control to 10.5% in intervention), and low birth weight by 30% (15% in control to 10.5% in intervention). We further hypothesised that household wealth and maternal education would modify the neonatal mortality responses with a greater reduction for women from the poorest households, and women with no education. We also hypothesised that the early start to IFA supplements would not increase iron-related side effects, e.g. nausea & vomiting in intervention clusters and will be cost-effective in reducing neonatal mortality in intervention clusters.

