#### Other measurements

Social, economic and demographic characteristics will be collected in a questionnaire collected at enrolment and will use standard demographic and health survey methods of an inventory of household assets to construct a wealth index, [16] as well as the socio-demographic characteristics of the mother.

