### Recruitment and consent of women

In the intervention clusters, SSs will make systematic door-to-door visits to identify new pregnancies through menstrual cycle tracking of all women of reproductive age. Once the woman reports a missed period, the SS will immediately notify the Field Implementers by mobile phone. The Field Implementers will then visit the pregnant mother along with the SS within the next 48 h to conduct a pregnancy test and enquire about the last menstrual period. If the pregnancy test is positive and the pregnancy is within the first trimester, the Field Implementers will register the mother and seek written consent. We will obtain written, witnessed informed consent from all participants.

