### Statistical analysis

Data analysis will be by intention to treat. We will conduct analyses at the infant level adjusted for the cluster randomisation. The primary analyses will compare the neonatal mortality rates and their 95% confidence intervals adjusted for clustering and groundwater iron level in each group. Secondary analyses will examine each outcome variable using separate mixed models. We will use Cox proportional hazards mixed models for mortality outcomes and include groundwater iron level as an interaction term in the mortality model. We will use population average Poisson model for other outcomes including preterm, small for gestation and low birth weights. Models will include treatment group as a fixed effect, community-cluster as a random effect to account for the cluster effect. The models will evaluate the impact of the interventions over time by testing for an interaction between time and intervention group. We will conduct analyses to identify the subgroups (based on household wealth, sex of infant and maternal education) that modify the response to the intervention. We will check the model assumptions and make appropriate adjustments to the analysis where necessary. Descriptive analysis will be performed to present the cause of death. We will compare the causes of death by sex of newborn, the time-period of death, and treatment arms (intervention Vs control). χ^2^ test or Fisher’s Exact test after adjusting for cluster effect will be used when appropriate. The economic analysis will estimate the incremental cost per life saved per year of the intervention over standard care. We will use sensitivity analyses of the findings to assess uncertainty in key parameters. Stata V.14 (StataCorp. 2015. Stata Statistical Software: Release 14. College Station, TX: Stata Corp LP.) will be used for all analyses.

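### The main mortality and birth-outcome models do not prespecify adjustment for household wealth or maternal education, although women are enrolled after unmasked cluster allocation

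*Protocol article*

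**What the plan says.** All references are to the protocol article.

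- **Statistical analysis, common model terms:** "Models will include treatment group as a fixed effect, community-cluster as a random effect to account for the cluster effect".
- **Statistical analysis, mortality:** the primary comparison of neonatal mortality rates is "adjusted for clustering and groundwater iron level in each group", and the Cox mixed models will "include groundwater iron level as an interaction term in the mortality model". The models also examine change over time by "testing for an interaction between time and intervention group".
- **Statistical analysis, other outcomes:** preterm delivery, small for gestation and low birth weight get a population-average Poisson model. No baseline covariate is named for it.
- **Statistical analysis, wealth and education:** these appear once, as effect modifiers: "We will conduct analyses to identify the subgroups (based on household wealth, sex of infant and maternal education) that modify the response to the intervention". Objectives and hypothesis gives the reason: "We further hypothesised that household wealth and maternal education would modify the neonatal mortality responses".
- **Other measurements:** an enrolment questionnaire supplies a household asset inventory for a wealth index, "as well as the socio-demographic characteristics of the mother".
- **Assignment of treatments:** clusters are allocated with stratification by Upazila, and the treatments cannot be masked.
- **Recruitment and consent of women:** after a positive test in the first trimester, "the Field Implementers will register the mother and seek written consent".
- **Early identification of pregnancy:** door-to-door detection, with a payment to village volunteers for finding pregnancies early, is described for the intervention clusters. The Control section says only that similar methods will be used there.

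**The concern.** Two baseline characteristics that the trial measures, and considers important enough to test as effect modifiers, do not enter the main treatment comparison.

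The first consequence is some lost precision. In a cluster trial, covariates that differ between areas can explain part of the between-cluster variance.

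The second matters more. Randomising clusters balances the populations living in them in expectation. It does not balance the women who enrol if enrolment depends on the arm. Here allocation is known before any woman is identified, entry is restricted to the first 90 days of gestation, and the intensity of early detection therefore affects who gets in. The Background reports any iron-folic acid use by 52% of rural women, 39% in the poorest households and 34% of women with no education. Contact with this kind of service thus already varies with both factors. If early detection reaches poorer or less educated women differently in the two arms, the unadjusted comparison carries that difference. Adjustment chosen after the imbalance has been seen is less convincing than adjustment fixed beforehand.

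**Working it through.** **1. Reproduce the stated sample size, to find the ICC to work with.** Inputs from Sampling frame and sample size: 33 against 24.8 deaths per 1000, 90% power, two-sided 5%, 50 clusters and 15,000 births per arm, so m = 300 per cluster.

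- Two-proportion formula, pooled variance: about 8,770 births per arm under individual randomisation.
- Design effect = 1 + (m − 1) × ICC.
- Printed ICC 0.0245: 1 + 299 × 0.0245 = 8.33. This needs 8,770 × 8.33 ≈ 73,000 births, or 243 clusters, per arm. With 15,000 per arm, power is 31%. The stated size is not reproduced.
- ICC 0.00245: 1 + 299 × 0.00245 = 1.73. This needs 8,770 × 1.73 ≈ 15,190 births, or 50.6 clusters, per arm. With 15,000 per arm, power is 89.6% for a 25% reduction and 80.8% for 22%. Both stated figures are reproduced.

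The precision gain is therefore worked at 0.00245. The share of cluster-mean variance lying between clusters is 299 × 0.00245 / 1.73 = 42%.

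**2. Precision gain for mortality.** The protocol gives no mortality by wealth or education, so prognostic strength is assumed: a ratio of mortality between the extreme wealth fifths of 1.5, 2 or 3 (log-linear across fifths, mean 28.9 per 1000), with 5% to 20% of that risk variance lying between clusters.

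With s² = 0.0289 × 0.9711 = 0.02807:

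- Variance of a cluster mean before adjustment: 0.00245 × s² + 0.99755 × s²/300 = 6.88×10⁻⁵ + 9.33×10⁻⁵ = 1.621×10⁻⁴.
- Worked case, ratio 2 with 10% between clusters: the SD of risk across fifths is 7.03 per 1000, so its variance is 4.94×10⁻⁵. Adjustment removes 0.10 × 4.94×10⁻⁵ from the first part and 0.90 × 4.94×10⁻⁵/300 from the second, leaving 1.570×10⁻⁴. The variance ratio is 0.969 and power is 90.5%.

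| Mortality ratio, extreme fifths (assumed) | Fall in variance | Power (89.6% without adjustment) | SD of chance imbalance, per 1000 |
|---|---|---|---|
| 1.5 | 0.6–2.1% | 89.8–90.2% | 0.19–0.37 |
| 2 | 1.6–6.2% | 90.1–91.4% | 0.32–0.63 |
| 3 | 4.0–15.2% | 90.8–93.8% | 0.51–0.99 |

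The last column is √[2 × (between part + within part/300)/50]. It ignores the Upazila stratification, so it errs on the high side. The target difference is 8.2 per 1000.

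**3. Size of a selection effect.** Suppose a share of one arm's enrolment shifts from the richest to the poorest fifth. Under the same assumed gradients, the extreme fifths differ by 11.7, 19.8 and 31.0 deaths per 1000 (for example 39.7 − 19.8 at ratio 2). Each percentage point shifted then moves that arm's expected mortality by about 0.12, 0.20 or 0.31 per 1000. The protocol gives no basis for the size or direction of any shift, and more births do not reduce it.

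**4. Birth outcomes.** With the protocol's ICC of 0.012 and m = 300, the design effect is 1 + 299 × 0.012 = 4.59 and the effective size is 15,000/4.59 ≈ 3,270 per arm. About 862 per arm would be needed for 15% against 10.5% at 80% power under individual randomisation. Power exceeds 99%, so the case for adjustment there rests on balance, not precision.

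**The case against.** **The mortality models are not bare.** A reader might infer from the quoted sentence that every model holds treatment and cluster alone. That is not so for mortality: groundwater iron is both an adjustment factor and an interaction term, and a time-by-treatment interaction is also named. The description fits only the birth-outcome models, as far as baseline covariates go.

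**There is protection against imbalance.** A reader might infer that there is none. With 100 clusters in 24 Upazilas, each stratum holds about four clusters, which restrains chance differences in area-level wealth and education. This objection stands for chance imbalance. It does not reach differential enrolment within clusters.

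**Effect modification is not prognosis.** The protocol expects wealth and education to change the response and links them to supplement use. It gives no mortality gradient for either. This stands, and it is why every gain above is conditional on an assumption.

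**Large gains at the printed ICC.** If wealth and education explained 10–40% of the between-cluster variance at an ICC of 0.0245, power would rise from about 32% to 34–45%. That is not credible. The between-cluster SD would be √(0.0245 × 0.033 × 0.967) = 28 per 1000, and explaining 40% of the variance would need these factors to move cluster risk by an SD of about 18 per 1000, over half the mean. Under the gradients assumed above, power at that ICC reaches at most 32.0%.

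**Selection is a recruitment question.** No passage shows selection on wealth or education, control pregnancies are to be found by similar methods, and the text does not say whether the volunteer payment also applies in control clusters. Adjusting for two measured variables would not cure selection on others. All of this stands; adjustment is a partial safeguard.

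**The covariate list may sit in the analysis plan.** It may, and that plan is not shown. The article does, however, state model terms and choose one adjustment factor, so the choice is open to comment. Its provision for adjustments where necessary follows the checking of model assumptions and names no covariates.

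**Conclusion.** As written, neither the primary mortality analysis nor the birth-outcome models adjust for household wealth or maternal education. Prespecifying both would be a modest improvement.

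On precision, expect 0 to 4 power points for mortality at an ICC of 0.00245, conditional on an assumed mortality ratio of 1.5 to 3 between extreme wealth fifths and 5–20% of that variance lying between clusters. For preterm delivery, power for the stated effect is already ample.

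The better argument is enrolment after open allocation, which cluster randomisation and Upazila stratification do not fully address. It identifies a vulnerability. The documents do not show that the arms will differ, and omitting these covariates does not itself bias the comparison if identification and consent are independent of arm.

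This is an optional, low-cost improvement. The protocol contains no error or contradiction on this point.

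**What to change.** Add one sentence to Statistical analysis: wealth index and maternal education enter as fixed covariates, alongside groundwater iron, in the primary mortality model, and as fixed covariates in the preterm and low-birth-weight models. The coding of each should be stated, and the estimate without these two covariates reported next to the adjusted one. If an analysis plan already lists them, a reference to it is enough.

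The sentence should be fixed before outcome data by arm are seen. No new data are needed: the enrolment questionnaire covers the household assets and the mother's socio-demographic characteristics, and the planned subgroup analyses already require both variables. The cost is a rule for a few missing values. The change does not replace comparing enrolment and baseline characteristics between the arms, since it addresses only selection that these two variables capture.

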### Data monitoring

#### Electronic data monitoring tool

We will develop an online monitoring system, which will provide us real-time information on enrolment status, adherence of the data collectors with the evaluation schedule and quality of data for key variables. This system will allow the field supervisors to monitor the performance of individual data collectors. All reports will be auto-generated from the system and will be available anytime for the investigators’ assessment.

#### Data safety and monitoring board

The research team will establish an independent data safety and monitoring board (DSMB) consisting of an independent paediatrician, a clinical trial specialist and a biostatistician. This DSMB is responsible for assessing the interim data, data quality, data completeness, adequacy of compliance with goals for recruitment and retention, and factors that might affect the study outcome or compromise the confidentiality of the trial data. Any unintended effects of trial intervention will also be notified to data safety and monitoring board.

#### Advisory committee

To facilitate the overall implementation process and to engage policymakers and other key decision makers, we will establish a national project advisory committee consisting of Ministry of Health and Family Welfare staff, staff, representatives from UNICEF, WHO, the Obstetric and Gynaecological, the Perinatal, and the Nutrition Societies of Bangladesh. This committee will assist in translating the Shonjibon study findings into policy. In addition, we will establish five district advisory committees consisting of local health officers, local government officials, local community groups, other relevant NGOs and project staff to help guide the research team.

### Access to data

All collected data will be accessible by the study investigators. All the investigators will have the right to analyse and publish data. We will only share datasets with all personally identifiable information removed, and every reasonable effort to keep the identification of study subjects in the strictest confidence.

### Dissemination plan

The research team will share the lessons learned from the study widely throughout Bangladesh and among global audiences. The authors will organise dissemination seminars to share the findings with all relevant stakeholders. We will present the intermediate and immediate results, which support the hypotheses generated from the trial, at national and international conferences and publish them in conference proceedings. We will publish the analysis of the outcomes in the form of internal documents, working papers, and in international peer-reviewed journals. Authorship eligibility will be based on recommendation from International committee for medical journals editors (ICMJE).

## Discussion

Iron deficiency is associated with increased risk of maternal death, preterm delivery, impaired foetal growth and development, low birth weight, increased neonatal mortality and impaired infant development [17]. In resource-poor countries, rates of maternal anaemia remain high. Although the importance of IFA supplements to prevent maternal anaemia and mortality is widely accepted, most antenatal IFA supplements distribution programs are of low priority. Evaluations of these programs using maternal anaemia as the outcome report little or no impact because of the multiple causes of maternal anaemia, low compliance, and inadequate distribution programs.

Recent surveys in Bangladesh indicate that only 52% of rural women reported any use of IFA supplements in their last pregnancy, but this falls to 39% for the poorest households, and to 34% for women with no education [5]. In the Projahnmo trial conducted in rural Bangladesh, only 40% of women in the baseline surveys reported any use of IFA supplements in pregnancy [18]. Access to IFA supplements is through antenatal care, however, in rural Bangladesh, the median gestation that women commence antenatal care is 5.2 months, and 44% of women report no use of antenatal care [5]. The Projahnmo trial demonstrated improved IFA supplements as 84% of pregnant women in the home-care treatment arm reported IFA supplements use in pregnancy [18]. Although they did not start early, these figures indicate there is a substantial opportunity to improve IFA supplements distribution in rural Bangladesh.

There is limited evidence about the optimal timing of IFA supplementation in pregnancy. Promising evidence came from a trial in China investigating the effects of IFA supplements in pregnancy on neonatal deaths [19]. However, the neonatal mortality analyses were post-hoc analyses, and the sample size was small resulting in poor precision in the effect estimates, and reduced power to explore all the factors modifying the effects on neonatal mortality. Thus, the impact of early IFA supplements on neonatal mortality needs confirmation in a larger scale trial.

This project will determine if antenatal IFA supplements commenced in the first trimester of pregnancy, rather than later, will significantly reduce neonatal deaths in the first month of life, and if this approach is cost-effective. It will also provide valuable evidence about the role of groundwater iron level in modifying the responses of antenatal IFA supplements on neonatal mortality since there is already some evidence which suggests a positive, dose-response association between natural iron in groundwater and the iron status of women [6].

## Abbreviation

ERC: Ethical Review Committee
HREC: Human Research Ethics Committee
IFA: Iron and folic acid
NHMRC: National Health and Medical Research Council
